# Checkpoint inhibition in combination with an immunoboost of external beam radiotherapy in solid tumors (CHEERS): study protocol for a phase 2, open-label, randomized controlled trial

**DOI:** 10.1186/s12885-021-08088-w

**Published:** 2021-05-07

**Keywords:** Head and neck squamous cell carcinoma, Melanoma, Non-small-cell lung carcinoma, Renal cell carcinoma, Transitional cell carcinoma, Immunotherapy, Checkpoint inhibitor, Stereotactic body radiotherapy, Survival, Clinical trial

## Abstract

**Background:**

While the introduction of checkpoint inhibitors (CPIs) as standard of care treatment for various tumor types has led to considerable improvements in clinical outcome, the majority of patients still fail to respond. Preclinical data suggest that stereotactic body radiotherapy (SBRT) could work synergistically with CPIs by acting as an in situ cancer vaccine, thus potentially increasing response rates and prolonging disease control. Though SBRT administered concurrently with CPIs has been shown to be safe, evidence of its efficacy from large randomized trials is still lacking. The aim of this multicenter randomized phase II trial is to assess whether SBRT administered concurrently with CPIs could prolong progression-free survival as compared to standard of care in patients with advanced solid tumors.

**Methods/design:**

Ninety-eight patients with locally advanced or metastatic disease will be randomized in a 1:1 fashion to receive CPI treatment combined with SBRT (Arm A) or CPI monotherapy (Arm B). Randomization will be stratified according to tumor histology (melanoma, renal, urothelial, head and neck squamous cell or non-small cell lung carcinoma) and disease burden (≤ or > 3 cancer lesions). The recommended SBRT dose is 24Gy in 3 fractions, which will be administered to a maximum of 3 lesions and is to be completed prior to the second or third CPI cycle (depending on CPI treatment schedule). The study’s primary endpoint is progression-free survival as per iRECIST. Secondary endpoints include overall survival, objective response, local control, quality of life and toxicity. Translational analyses will be performed using blood, fecal and tissue samples. *Discussion:* The CHEERS trial will provide further insights into the clinical and immunological impact of SBRT when combined with CPIs in patients with advanced solid tumors. Furthermore, study results will inform the design of future immuno-radiotherapy trials.

**Trial registration:**

Clinicaltrials.gov identifier: NCT03511391. Registered 17 April 2018.

**Supplementary Information:**

The online version contains supplementary material available at 10.1186/s12885-021-08088-w.

## Background

Recently, checkpoint inhibitors (CPIs) have become the standard of care (SOC) as a first or second line systemic treatment for patients with inoperable or metastatic non-small cell lung cancer, renal cell cancer, urothelial cancer, melanoma and head and neck cancer [1–4]. Unfortunately, the majority of patients do not respond to this treatment and the overall survival (OS) remains limited. Patients who do not respond to CPIs typically have less immunogenic tumors with low levels of tumor-infiltrating cluster of differentiation 8 positive (CD8+) T cells [5, 6]. It is possible that in these non-responding patients, the tumor microenvironment hinders T-cell infiltration and induction of an endogenous immune response.

Pre-clinical and clinical evidence indicate that radiotherapy can act as an in-situ cancer vaccine by inducing immunogenic cell death, triggering the release of tumor-derived antigens and attracting CD8+ T cells to the tumor and hereby leading to an increase in immunogenicity. This can in turn elicit a – potentially systemic – anti-tumor immune response [7–10], which may lead to tumor responses outside the irradiated regions, a phenomenon called the “abscopal” effect, as previously reported in several kinds of malignancies [11–15]. Pre-clinical evidence indicates that hypofractionated radiotherapy (e.g. 3 × 8 Gy) might be best suited to trigger systemic immune effects [16]. Stereotactic body radiotherapy (SBRT) is an innovative technique which allows the safe administration of this hypofractionated radiotherapy with high precision and limited toxicity.

The combination of CPIs with SBRT could therefore work synergistically and lead to an improved systemic immune response, with higher response rates and longer OS as a result [7–9, 11]. Apart from a systemic abscopal effect, clinical evidence also indicates that the combination of radiotherapy with CPIs leads to excellent local responses of irradiated tumors, denoted as the “adscopal” effect [8].

Early phase clinical trials have demonstrated that CPIs can be combined safely with radiotherapy without excess toxicity [8, 9]. In our center, we have conducted 2 phase I trials and 1 phase II trial combining CPIs with SBRT [17–19]. We did not observe additional toxicity with the combined use of CPIs with SBRT. The current randomized trial will shed light on the efficacy of this combination treatment.

## Methods/design

This study is approved by the Ghent University Hospital Ethics committee (EC2017/1678) and is registered on clinicaltrials.gov (NCT03511391). Patients diagnosed with locally advanced or metastatic melanoma, renal cell carcinoma, non-small cell lung carcinoma, urothelial carcinoma or head- and neck squamous cell carcinoma will be entered in a randomized phase II trial. In the interventional arm A, patients will undergo SBRT to maximally three extracranial lesions in addition to SOC CPI treatment. Patients in the control arm B will only receive SOC CPIs (Fig. 1).

**Fig. 1 Fig1:**
[figure not shown]
CHEERS trial design. CPI, checkpoint inhibitor; HNSCC, head and neck squamous cell carcinoma; NSCLC, non-small cell lung carcinoma; RCC, renal cell carcinoma; SBRT, stereotactic body radiotherapy; SOC, standard of care; UC, urothelial carcinoma. Brown vial, fecal sample; red vial, blood sample; lightning bolt, radiotherapy fraction

### Objectives

Primary endpoint:
Progression-free survival (PFS) will be analyzed in all patients who received at least one cycle of CPIs. PFS is defined as the time from randomization to disease progression or death from any cause. Disease progression will be evaluated using systemic imaging by computed tomography (CT) or positron emission tomography (PET) CT and will be defined according to immune Response Evaluation Criteria in Solid Tumors (iRECIST) [20]. Imaging will occur every 3 months, or earlier if clinically indicated.Secondary endpoints:
Overall survival (OS) is defined as the time from trial randomization to the date of death from any cause.Best objective overall response as per iRECIST and RECIST 1.1 [21].Local control of the irradiated lesion(s) will be assessed per RECIST 1.1.Adverse events will be scored using the Common Terminology Criteria for Adverse Events (CTCAE) version 5.0.Quality of life (QOL) scoring using the EORTC QLQ-C30. Raw scores will be transformed to a linear scale ranging from 0 to 100. The results will be presented in accordance with the most recent guidelines for reporting health related QOL randomized controlled trials.Systemic responses during the trial will be assessed using peripheral blood samples. Using flow cytometry, subsets of immune cells, selected immune checkpoints and cell death markers will be identified. Cytokines will be measured via multiplex analysis. Cell-free DNA will be analyzed using shallow whole genome sequencing which will allow reliable non-invasive copy-number profiling, as previously demonstrated by our group [22]. In addition, germline DNA and circulating extracellular RNA will be analyzed. If at any point prior to or during the study, tissue samples of the primary tumor or metastatic foci were obtained from the trial patient for diagnostic purposes and stored, any remaining tissue may be retrieved from the respective pathology department. Analyses of this formalin-fixed paraffin embedded (FFPE) material will include isolation of tumor RNA and DNA, programmed death-ligand 1 (PD-L1) expression and tumor infiltrating lymphocytes (TIL). Depending on the published scientific literature available at the time of data cut off, additional analyses could be performed.The predictive and prognostic value of the composition of the gut microbiome will be assessed using a serial fecal sampling.

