#### Evaluation and randomization

Patients must be restaged within 4 weeks prior to randomization. The study will employ a 1:1 randomization between arm A: arm B, stratified on primary tumor histology (melanoma, renal cell carcinoma, non-small-cell carcinoma, urothelial carcinoma or head-and-neck squamous cell carcinoma) and on the number of metastases present at the time of inclusion (≤3 or > 3). Randomly permutated blocks of variable length 2 and 4 will thus be assigned to each stratum. Within each block, assignment to treatment and control is random but balanced. Every patient is assigned a treatment arm following the randomization-scheme. As this is an open-label trial, the randomization procedure and outcome will not be blinded.

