## Statistical analysis

### Sample size

This trial is designed to assess whether SBRT to maximum 3 lesions after 2 cycles of CPIs could prolong PFS as compared to standard of care in metastatic patients. The study has a two-sided 0.05% type I error and 80% power to detect an improvement in PFS of 3 months in the intervention group as compared to the control group using a stratified log-rank test. Median PFS for the control arm was estimated at 3.1 months. Median PFS after initiation of CPIs is approximately as follows:
20% metastatic melanoma (1st-3rd line): 5.2 months [1, 4, 24–26]20% renal cell carcinoma (2nd line): 4.6 months [27]20% non-small cell lung carcinoma (2nd-3rd line): 2.7 months [3, 28, 29]25% bladder cancer (1st-3rd line): 2.2 months [2, 30]15% head- and neck cancer (1st-2nd line): 2.0 months [31, 32]

We estimate to recruit 30% oligometastatic patients (defined as ≤3 metastases) and 70% non-oligometastatic (defined as > 3 metastases) in the trial. We hypothesize that an improved PFS of 3 months will be seen. We chose for a 36 month accrual time and a 12 month follow-up time. Analysis is planned 9 months after inclusion of the last patient.

Using these assumptions and including a 5% at random dropout rate, the trial requires a total of 98 patients to be randomized in to two groups. Sample size calculation was performed using R version 3.4.1.

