### Data analysis and monitoring

Patients will be analyzed according to the group to which they were assigned (intention-to-treat). Descriptive statistics will be used to summarize patient characteristics per treatment group.

PFS will be defined as the time from randomization to disease progression (as per iRECIST using CT or PET/CT) or death from any cause. PFS will be compared between groups using the stratified log-rank test. Kaplan-Meier estimates of 1-year PFS and OS will be provided for each treatment group and as a post-hoc subgroup analysis based on patient characteristics described above. Median follow-up time will be derived using both complete and incomplete follow-up times. Cox proportional hazards regression will be used to provide hazard ratio estimates when assessing PFS using covariates of interests. A *p*-value of less than 0.05 will be considered statistically significant.

For the evaluation of biomarkers on one time point, differences between groups will be tested using the Mann-Whitney U test. For the evaluation of biomarkers over time, differences between groups will be tested using the Wilcoxon signed-rank test. To evaluate correlations, Spearman correlation coefficients will be calculated. A p-value of less than 0.05 will be considered statistically significant.

All statistical analyses will be performed using SPSS (SPSS Inc., Chicago, Il, USA). RNA sequencing data will be analyzed using dedicated pipelines. Further processing of the count tables will be performed in R (v.3.5.1).

In order to avoid introducing bias no interim analysis will be performed. Early trial termination may be deemed necessary in case of poor accrual. As the experimental treatment carries minimal risks, no data monitoring committee will be implemented, nor will there be a predefined stopping procedure.

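### The primary PFS population is defined two ways (at least one CPI cycle versus intention-to-treat), so a few patients could be excluded after a known allocation; any bias is probably small, but the text must be reconciled

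*Protocol article*

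**What the plan says.** Under Objectives, the primary endpoint opens with a population rule: "Progression-free survival (PFS) will be analyzed in all patients who received at least one cycle of CPIs". The next sentence fixes the clock: "PFS is defined as the time from randomization to disease progression or death from any cause".

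Under Data analysis and monitoring, the population is described differently: "Patients will be analyzed according to the group to which they were assigned (intention-to-treat". The stratified log-rank test of PFS follows in the same section, with no carve-out for patients who never received a CPI. The term modified intention-to-treat does not appear, and no other section reconciles the two statements.

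Two further facts bear on the point. The study calendars (Tables 1, 2 and 3) put allocation in the column for days -14 to -1, before the first dose in cycle 1. On blinding, Evaluation and randomization says: "As this is an open-label trial, the randomization procedure and outcome will not be blinded".

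**The concern.** A patient can be randomised, learn the arm, and never receive a CPI. The Objectives rule drops that patient from the primary analysis; the intention-to-treat rule keeps the patient in the assigned arm. Because time runs from randomisation, a death or progression in such a patient is an early event under one rule and does not exist under the other.

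Two things are at stake. First, a set defined by what happens after randomisation is no longer fully protected by it, and here the exclusion can occur with the allocation known. Second, two admissible primary datasets leave room for a choice after open-label data have accumulated. The restriction also buys little: CPI is given in both arms and SBRT comes only before the second or third cycle (Interventions), so one CPI cycle does not identify the patients who received the treatment under test.

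**Working it through.** **1. Do the two sets differ?**

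| Patient | Objectives rule | Intention-to-treat rule |
|---|---|---|
| Randomised, at least one CPI cycle | included | included |
| Randomised, no CPI, early event | excluded | event in assigned arm |
| Randomised, no CPI, withdraws at once | excluded | censored near time zero |

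The sets differ by exactly the non-starters. The article gives no count of them.

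**2. The plan's own figure, and whether it depends on the choice.** Inputs from Sample size: "Median PFS for the control arm was estimated at 3.1 months", a gain of 3 months, 80% power, 5% at-random dropout and 98 randomised. On timing: "We chose for a 36 month accrual time and a 12 month follow-up time", although analysis at 9 months after the last inclusion is also stated, so both were tried. The type I error is printed as 0.05%, but the analysis section uses 0.05. I used two-sided 5%, the only level tried that reproduces N; the misprint is a separate matter.

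- HR = 3.1 / (3.1 + 3) = 0.508, assuming exponential PFS.
- Schoenfeld: d = 4(1.960 + 0.842)² / (ln 0.508)² = 69 events, which gives 76 to 77 patients with dropout. This does not give 98.
- Simulating the stated test over 10 strata (five histologies by two burden levels, 6,000 runs) gives 80.4% power at 93 patients with 9 months' follow-up and 80.8% with 12 months. Then 93 / 0.95 = 97.9, or 98. The stated figure is reproduced.

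The 98 counts randomised patients with dropout already allowed for, so an all-randomised primary set leaves it unchanged.

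**3. Worst-case shift (assumption: four non-starters, all in one arm, all with early events).**

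- Events: 93 × 0.948 = about 88 (analysis 9 months after last inclusion). Log-rank variance V = 88 / 4 = 22.
- Score change per early event removed from one arm = 1 − n₁/n = about 0.5. This is the most one patient can contribute; a later event moves the score less.
- Four events: score change 4 × 0.5 = 2.
- Log HR: 2 / 22 = 0.091, or about 9% to 10% on the HR scale. Z: 2 / √22 = 0.43.
- With 94.6 events instead (98 patients, 12 months, no dropout): V = 23.65, giving 0.085 and 0.41, so the result is not sensitive to the event count.
- Four patients are 4 / 49 = 8% of one arm.

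V = d/4 ignores the information lost in ten small strata, so these are approximations. The simulation in step 5 uses the stratified test itself.

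**4. Benign cases.** Two early events lost from each arm: 2 × 0.5 − 2 × 0.5 = 0. Non-starters who would be censored almost at once contribute no event, so removing them changes the score by almost nothing.

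**5. Simulation of both extremes at N = 98 (the numbers excluded are assumptions).**

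| Random exclusion, both arms | 0% | 2% | 5% | 10% |
|---|---|---|---|---|
| Power | 83% | 82% | 81% | 78% |

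| Earliest failures removed from one arm only, under the null | 0 | 1 | 2 | 3 | 5 |
|---|---|---|---|---|---|
| Two-sided type I error | 5.5% | 5.8% | 6.3% | 7.4% | 9.7% |

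The second table used 4,000 runs. The standard error near 5.5% is √(0.0545 × 0.9455 / 4000) = 0.36 percentage points, so one or two removals cannot be clearly told apart from none.

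**The case against.** The two sentences can be read together. The analysis section may fix only the arm in which a patient is counted, and the Objectives section which patients enter. That gives a modified intention-to-treat set without the label. The excluding event is also largely unrelated to the randomised treatment: CPI is standard of care in both arms, being due to receive it is an inclusion criterion, and SBRT comes only after one or two cycles. Both arms therefore have the same plan through the first dose. The window is at most 14 days and Karnofsky status must exceed 60. A statistical analysis plan, not shown here, may settle the set.

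Most of this stands as to size: few exclusions are likely, and there is no evident reason for a strong imbalance. It does not remove the contradiction. The combined reading is not written anywhere, and it would still exclude patients after a known allocation under an intention-to-treat label. Nor is this a detail left to another document, because the article itself states two rules.

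A reader might go further and infer that non-starters are mainly patients who deteriorate, die or withdraw on learning their arm. The article gives no reasons for not starting, so this is unsupported; those who withdraw would mostly be censored at once and would hardly affect the test. A reader might also treat four lost patients as falling within the planned 5% dropout. That allowance is for random dropout across the trial, whereas four losses confined to one arm are 8% of it.

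**Conclusion.** The inconsistency is real and concerns the primary analysis, so it should be resolved before the data are examined. Its likely numerical effect is small and its direction unknown: removing early events from arm A favours SBRT, and removing them from arm B does the opposite. The shift of about 0.09 on log HR and 0.43 on Z rests on an assumed four early events, all lost from one arm, and is an unlikely worst case. Under balanced loss or immediate censoring it is close to zero, and random exclusion of 5% costs about 2 points of power. The documents do not support saying that the primary p-value will be materially biased, or that anyone intends to choose between datasets. They support saying that the text permits both. No sample-size figure depends on the point. Severity: moderate.

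**What to change.** Replace the population sentence under Objectives with: *PFS is analysed in all randomised patients, in the arm assigned, whether or not CPI or SBRT was started.* Keep following non-starters for progression and survival so that their outcomes are observed. Report the set with at least one CPI cycle as a labelled sensitivity analysis, with the number of non-starters and their reasons by arm.

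A clearly declared modified intention-to-treat set would also end the contradiction, but it would keep the post-randomisation exclusion for no evident gain. The cost is one sentence and the follow-up of a few patients; N stays at 98.

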#### Inclusion criteria

Before patient registration, written informed consent must be given according to ICH/GCP and national/local regulations.Histologically confirmed diagnosis of a solid tumor.At least one extracranial tumor lesion available for radiotherapy administration.Patient will receive a checkpoint inhibitor per standard of care in one of the following settings (locally advanced or metastatic):
melanoma: 1st-3rd line nivolumab or pembrolizumabrenal cell carcinoma: 2nd line nivolumabnon-small cell lung carcinoma: 2nd or 3rd line nivolumab, atezolizumab or pembrolizumaburothelial carcinoma: 1st-3rd line nivolumab, atezolizumab or pembrolizumabhead- and neck squamous cell carcinoma: 1st-2nd line pembrolizumab, 2nd line nivolumabKarnofsky Performance status > 60Age 18 years or older.

#### Exclusion criteria

Prior radiotherapy preventing treatment with SBRT.Prior treatment with an anti-PD-(L)1 antibody.Has a known additional malignancy that is progressing or requires active treatment. Exceptions include basal cell carcinoma of the skin or squamous cell carcinoma of the skin that has undergone potentially curative therapy or in situ cervical cancer or prostate cancer that has undergone potentially curative therapy and with normalized PSA.Uncontrolled central nervous system (CNS) metastases at baseline (controlled = previously-treated CNS metastases (surgery ± radiotherapy, radiosurgery, or gamma knife) and who meet both of the following criteria: a) are asymptomatic and b) have no requirement for steroids or enzyme-inducing anticonvulsants), and/or carcinomatous meningitis.Any condition requiring systemic treatment with corticosteroids (> 10 mg daily prednisone equivalent) or other immunosuppressive medication within 14 days prior to the first dose of study drug. Inhaled steroids and adrenal replacement steroid doses > 10 mg daily prednisone equivalent are permitted in the absence of active autoimmune disease.Has a diagnosis of immunodeficiency or history of human immunodeficiency virus (HIV), Hepatitis B or Hepatitis C infection.Mental condition rendering the patient unable to understand the nature, scope and possible consequences of the study.Patient not likely to comply with the protocol; i.e. uncooperative attitude, inability to return for follow-up visits or unlikely to complete the study.Contraindication for radiotherapy.Female subjects of childbearing potential must be willing to use an adequate method of contraception for the course of the study through 120 days after the last dose of study medication.

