#### Study calendar

Baseline/pre-study evaluations:
Documentation of the patient’s medical history and all medicationRegistration of baseline symptoms/toxicity and QOLKarnofsky Performance statusClinical examinationBlood draw assessing at least the following elements: complete blood count (hemoglobin, white blood cell count and formula, thrombocyte count), electrolytes (sodium, potassium), renal function (creatinine, blood urea nitrogen), liver function (alanine aminotransferase, aspartate aminotransferase, gamma-glutamyltransferase, alkaline phosphatase), lactate dehydrogenase and C-reactive protein.

Baseline evaluations are to be conducted within 2 weeks prior to start of checkpoint inhibitors.

During study:
Registration of symptoms before first cycle of checkpoint inhibitors, at start of radiotherapy and at end of radiotherapy (if applicable) and at least every 4 weeks until 4 months after randomization. Toxicity will be assessed using the CTCAE version 5.0.QOL will be assessed at baseline, at first evaluation and every 6 months thereafter. QOL will be assessed using the QLQ-C30 questionnaire.A fecal sample will be obtained prior to start of CPI treatment and at the first evaluation.Blood samples (EDTA and serum) for immunological analysis will be obtained prior to start of CPIs, before first fraction (Arm A), before the second/third cycle of CPIs and at every evaluation (consultation after imaging) as long as patient receives CPI (i.e. liquid biopsy).Patients will be followed up until disease progression defined as per iRECIST.Off-study and follow-up evaluationsOnce a subject experiences confirmed disease progression, the subject moves into the survival follow-up phase and should be contacted by telephone every 12 weeks to assess for survival status until death, withdrawal of consent or the end of the study, whichever occurs first.Monitoring of progression and survival.

Study calendars for different CPI treatment schedules are represented in Tables 1, 2, and 3.

**Table 1 Tab1:** Study calendar for nivolumab 2-weekly: SBRT prior to C3; first evaluation after C5

	STUDY PERIOD											
	Enrolment	Allocation	Post-allocation								Close-out	Long-term follow-up
**TIMEPOINT**	**Pre-study**	**D-14 to -1**	**C1D1**	**C2D1**	**C3D-6**	**C3D-4 or -3**^**a**^	**C3D-1**	**C3D1**	**C4D1**	**C5D1**	**C5D +1 to +14**	**Every evaluation**^b^

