**ENROLMENT**												
Eligibility screen	X											
Informed consent	X											
Allocation		X										

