**ASSESSMENTS**												
Demographics, medical Hx, performance status	X											
Imaging (CT or PET/CT)	X										X	
Fecal sample			X								X	
Liquid biopsy			X		X^c^			X				X
Adverse events			X	X	X^c^			X	X	X	X	X^d^
Quality of life			X									X^e^

*C* cycle; *CT* computed tomography; *D* day; *Hx* history; *PET* positron emission tomography; *q2w* 2-weekly; *SBRT* stereotactic body radiotherapy

^a^ SBRT is given on Wednesday-Friday-Monday or Friday-Monday-Wednesday, depending on whether nivolumab is administered on Tuesday or Thursday, respectively

^b^ Consultation after imaging; until disease progression as per iRECIST

^c^ Only for patients in study arm A

^d^ Until 3 months after radiotherapy

^e^ At least every 6 months

**Table 2 Tab2:** Study calendar for nivolumab 4-weekly: SBRT prior to C2; first evaluation after C3

	STUDY PERIOD									
	Enrolment	Allocation	Post-allocation						Close-out	Long-term follow-up
**TIMEPOINT**	**Pre-study**	**D-14 to -1**	**C1D1**	**C2D-6**	**C2D-4 or -3**^**a**^	**C2D-1**	**C2D1**	**C3D1**	**C3D +1 to +14**	**Every evaluation**^b^

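### The steroid and immunosuppressant exclusion is timed from the first dose, up to 14 days after open allocation, so the pre-allocation eligibility screen cannot settle it

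*Protocol article*

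**What the plan says.** The protocol article uses two time anchors for entry to the trial.

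- **First dose.** The steroid and immunosuppressant exclusion (Exclusion criteria) covers such treatment "or other immunosuppressive medication within 14 days prior to the first dose of study drug". The Study calendar adds: "Baseline evaluations are to be conducted within 2 weeks prior to start of checkpoint inhibitors". Its list of these evaluations includes baseline symptoms and Karnofsky status, and Karnofsky status is also an inclusion criterion.
- **Randomisation.** Under Evaluation and randomization: "Patients must be restaged within 4 weeks prior to randomization".

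Tables 1 to 3 share one layout: a Pre-study column, then an allocation column headed D-14 to -1, then cycle 1 day 1 (C1D1). The rows "Eligibility screen" and "Demographics, medical Hx, performance status" are marked in the Pre-study column. Adverse events are first marked at C1D1.

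Allocation is open: "As this is an open-label trial, the randomization procedure and outcome will not be blinded".

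Two statements define who is analysed. Objectives says "Progression-free survival (PFS) will be analyzed in all patients who received at least one cycle of CPIs". Data analysis and monitoring says "Patients will be analyzed according to the group to which they were assigned (intention-to-treat").

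**The concern.** An eligibility criterion should be decidable from what is known when the patient is randomised. A look-back that ends at a future dosing date is not. A patient can satisfy every criterion at screening, be allocated openly, start a disqualifying drug in the following days, and then be in breach of the criterion as worded. Whoever decides what happens next knows the arm.

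The stake is the primary comparison. Progression-free survival (PFS) is counted from randomisation, and patients who newly need steroids may well have a poorer outlook than the rest. If some are never dosed, and so drop out of the PFS analysis, the loss need not be neutral between arms. A baseline symptom grade taken once the arm is known is open to a similar, smaller influence.

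**Working it through.** The plan states no figure on this point, so there is none to reproduce. The check overlays the windows and then follows a patient through the analysis rules.

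**Inputs**
- Look-back: 14 days before first dose, that is D-14 to D-1 (Exclusion criteria). Study drug is read here as the checkpoint inhibitor (CPI), first given at C1D1.
- Allocation: day D-k, with k from 1 to 14 (Tables 1 to 3).
- Baseline evaluations: the same two weeks before CPI start (Study calendar).

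**1. Look-back days after allocation.** For allocation on D-k, the days strictly after allocation and before the dose number k - 1.

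| Allocation day | Days after allocation | Share of 14 |
|---|---|---|
| D-1 | 0 | 0% |
| D-7 | 6 | 6/14 = 43% |
| D-14 | 13 | 13/14 = 93% |

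If all 14 allocation days are equally likely (an assumption), the mean is (0 + 1 + ... + 13)/14 = 91/14 = 6.5 days. Counting the allocation day itself gives 1 to 14 days, mean 7.5. With the window counted back from randomisation, the figure is 0 for every patient.

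**2. Baseline evaluations.** For allocation on D-k, 14 - k days lie inside the two-week window and before the allocation day. That is 7 days for D-7, 1 day for D-13 and none for D-14. At D-14 a Karnofsky assessment meets both the Pre-study marking and the two-week rule only if done on the allocation day. Elsewhere a site has at least one earlier day, so the conflict is confined to D-14 and its immediate neighbours. Baseline symptoms differ: their first mark in the tables is C1D1, which follows allocation for everyone.

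**3. Consequence for a patient who breaches the criterion after allocation**
- If dosed anyway, the patient is in the PFS analysis under both statements, although in literal breach of an exclusion.
- If not dosed, the patient is out under Objectives, because no CPI cycle was received, and in under Data analysis and monitoring, because the patient was assigned.

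The second branch is where the timing anchor can reach the primary endpoint. It needs both the first-dose anchor, which supplies a protocol-based reason not to proceed, and the treated-only population, which turns that into loss from the analysis.

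**The case against.** The strongest reply is that the calendars already settle eligibility before allocation. All three tables mark the eligibility screen, history and performance status as Pre-study, and nothing in the article orders a re-check afterwards or tells sites to declare a randomised patient a screen failure. This stands against the broader reading that a reader might infer, namely that the plan decides eligibility after the arm is known. The document does not say so. It does not rescue the steroid criterion, because a screen held before allocation cannot verify a window that ends at a later dose.

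A second reply is that the two-week rule on baseline evaluations permits assessment after allocation but does not require it, and is not an eligibility rule. That stands for Karnofsky status, apart from the edge at D-14. Baseline symptoms are not an eligibility criterion either, so their timing is a measurement point only.

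A third reply is that no bias has been shown. From allocation to C1D1 both arms follow the same schedule, since radiotherapy comes only before cycle 2 or 3, so nothing scheduled in the gap would make steroid use differ by arm. The conflict between the treated-only population and intention-to-treat also exists whatever the steroid anchor. Both remarks are fair. They leave arm-dependent loss as a possibility that the wording allows, and they show that re-anchoring the window is not enough by itself.

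Lastly, handling of patients found ineligible commonly sits in the full protocol or analysis plan, and its absence here is no finding. The point rests only on what the article states: a first-dose anchor, an earlier open allocation and two incompatible analysis populations.

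**Conclusion.** The point holds as a mismatch of time anchors with a route to the primary endpoint. As worded, 0 to 13 of the 14 look-back days (0% to 93%) fall after open allocation, and the criterion cannot be fully verified at the screen. The range rests on counting days strictly after allocation and on reading study drug as the CPI; the mean of 6.5 days also assumes equally likely allocation days.

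A share of days is not a measure of bias. The document gives no rate of steroid starts between allocation and first dose, and none for patients left undosed, so neither a number of patients nor a direction of bias can be derived. Two further inferences are unsupported: that the whole window can lie after randomisation (at D-14 it is 13 of 14 days), and that Karnofsky status is generally assessed after allocation.

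Sample size, type I error and power are unaffected.

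**What to change.** 1. In Exclusion criteria, count the 14-day look-back from randomisation. The steroid threshold is unchanged.
2. In Study calendar and Tables 1 to 3, time the eligibility and baseline symptom assessments from randomisation, and complete them before allocation is released.
3. State that a change in status between randomisation and first dose does not make a randomised patient ineligible for analysis. Whether and when to start the CPI is left as it is now.
4. Reconcile Objectives with Data analysis and monitoring so that all randomised patients stay in the primary PFS analysis. Without this step, undosed patients still drop out however the window is anchored.

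The cost is protocol wording. Tests done up to 14 days before randomisation, with randomisation up to 14 days before C1D1, can be 14 + 14 = 28 days old at first dose, against 14 now, so up to 14 days older. Routine pre-dose bloods can still be drawn under standard of care.
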